| Number of Participants with Rationale                                 | Postoperative wound problems occur in at least 5% percent of all interventions. Incidence for both, revision surgery and/or SSI, in our selected patient population is set for 10%. We perform a superiority RCT with a power of 80% in favor of the decolonization. With event-free surgeries to 95% in the decolonization arm versus 90% in the standard arm, we formally need 2 x 474 surgery episodes, which we sum up to 2 x 500 surgeries (n = 1'000). A patient can be included several times as long as he/she gets not infected.

At the Balgrist, we perform at least 5000 surgical operations per year (in reality more than 6000). With a very conservative estimation, we see at least 600 surgical episodes per year (12% of surgeries) that can be included; mostly because of the advanced age, diabetes, and high ASA-Scores of our patients. The interventional part of the trial lasts two years; with interim analysis after 1 year (+/- 2 months). An independent advisory board might stop the trial. For the secondary outcomes (adverse events, questionnaire), we do not require a minimal sample size. |                            |                            |          |          |             |          |          |          |                              |              |                            |                            |                     |       |       |   |               |       |       |       |                          |        |        |        |                      |       |       |       |                  |       |     |       |                           |               |               |               |
| GCP Statement                                                         | This study will be conducted in compliance with the protocol, the Declaration of Helsinki, the ICH-GCP and national legal and regulatory requirements.                                                                                                                                                                                                                                                                                                                                                                                                                                                                                                                                                                                                                                                                                                                                                                                                                                                                                                                                                                                 |                            |                            |          |          |             |          |          |          |                              |              |                            |                            |                     |       |       |   |               |       |       |       |                          |        |        |        |                      |       |       |       |                  |       |     |       |                           |               |               |               |
| Statistical analyses                                                  | Group comparisons by Pearson-Chi  -test or the Wilcoxon-ranksum-tests. Multivariate adjustments by Cox regression without cluster analysis. Stratifications according to the type of surgery. We will perform Intention-to-Treat and Per-Protocol analyses.                                                                                                                                                                                                                                                                                                                                                                                                                                                                                                                                                                                                                                                                                                                                                                                                                                                                |                            |                            |          |          |             |          |          |          |                              |              |                            |                            |                     |       |       |   |               |       |       |       |                          |        |        |        |                      |       |       |       |                  |       |     |       |                           |               |               |               |
| Budget                                                                | 

Costs (cost-covering)	Total	1st Year	2nd Year	

a. Ethical Comittee	3,000	3,000	0	

b. Monitoring	5,000	2,500	2,500	

c. Nurse 20% for 2 years	39,000	19,500	19,500	

d. Social securities	5,654	2,827	2,827	

e. Miscellaneous	2,346	423	1,923	

Swiss Francs (CHF)	55,000	28,250	26,750	

                                                                                                                                                                                                                                                                                                                                                                                                                                                             |                            |                            |          |          |             |          |          |          | Costs (cost-covering) | Total | 1st Year | 2nd Year | a. Ethical Comittee | 3,000 | 3,000 | 0 | b. Monitoring | 5,000 | 2,500 | 2,500 | c. Nurse 20% for 2 years | 39,000 | 19,500 | 19,500 | d. Social securities | 5,654 | 2,827 | 2,827 | e. Miscellaneous | 2,346 | 423 | 1,923 | Swiss Francs (CHF) | 55,000 | 28,250 | 26,750 |
| Costs (cost-covering)                                                 | Total                                                                                                                                                                                                                                                                                                                                                                                                                                                                                                                                                                                                                                                                                                                                                                                                                                                                                                                                                                                                                                                                                                                           | 1st Year | 2nd Year |          |          |             |          |          |          |                              |              |                            |                            |                     |       |       |   |               |       |       |       |                          |        |        |        |                      |       |       |       |                  |       |     |       |                           |               |               |               |
| a. Ethical Comittee                                                          | 3,000                                                                                                                                                                                                                                                                                                                                                                                                                                                                                                                                                                                                                                                                                                                                                                                                                                                                                                                                                                                                                                                                                                                                  | 3,000                      | 0                          |          |          |             |          |          |          |                              |              |                            |                            |                     |       |       |   |               |       |       |       |                          |        |        |        |                      |       |       |       |                  |       |     |       |                           |               |               |               |
| b. Monitoring                                                                | 5,000                                                                                                                                                                                                                                                                                                                                                                                                                                                                                                                                                                                                                                                                                                                                                                                                                                                                                                                                                                                                                                                                                                                                  | 2,500                      | 2,500                      |          |          |             |          |          |          |                              |              |                            |                            |                     |       |       |   |               |       |       |       |                          |        |        |        |                      |       |       |       |                  |       |     |       |                           |               |               |               |
| c. Nurse 20% for 2 years                                                     | 39,000                                                                                                                                                                                                                                                                                                                                                                                                                                                                                                                                                                                                                                                                                                                                                                                                                                                                                                                                                                                                                                                                                                                                 | 19,500                     | 19,500                     |          |          |             |          |          |          |                              |              |                            |                            |                     |       |       |   |               |       |       |       |                          |        |        |        |                      |       |       |       |                  |       |     |       |                           |               |               |               |
| d. Social securities                                                         | 5,654                                                                                                                                                                                                                                                                                                                                                                                                                                                                                                                                                                                                                                                                                                                                                                                                                                                                                                                                                                                                                                                                                                                                  | 2,827                      | 2,827                      |          |          |             |          |          |          |                              |              |                            |                            |                     |       |       |   |               |       |       |       |                          |        |        |        |                      |       |       |       |                  |       |     |       |                           |               |               |               |
| e. Miscellaneous                                                             | 2,346                                                                                                                                                                                                                                                                                                                                                                                                                                                                                                                                                                                                                                                                                                                                                                                                                                                                                                                                                                                                                                                                                                                                  | 423                        | 1,923                      |          |          |             |          |          |          |                              |              |                            |                            |                     |       |       |   |               |       |       |       |                          |        |        |        |                      |       |       |       |                  |       |     |       |                           |               |               |               |
| Swiss Francs (CHF)                                                    | 55,000                                                                                                                                                                                                                                                                                                                                                                                                                                                                                                                                                                                                                                                                                                                                                                                                                                                                                                                                                                                                                                                                                                                          | 28,250              | 26,750              |          |          |             |          |          |          |                              |              |                            |                            |                     |       |       |   |               |       |       |       |                          |        |        |        |                      |       |       |       |                  |       |     |       |                           |               |               |               |
| Payment of donation                                                   | Installments in February 2023 to Balgrist funding account: 

Swiss Francs (CHF) 47,500 – Schülke Switzerland

Installments in 2024 to third party funding account (End of Trial): CHF 7.500 – Schülke Switzerland

 The 550 sets (500 for the study, 50 in reserve) are provided by Schülke Switzerland                                                                                                                                                                                                                                                                                                                                                                                                                                                                                                                                                                                                                                                                                                                                                                             |                            |                            |          |          |             |          |          |          |                              |              |                            |                            |                     |       |       |   |               |       |       |       |                          |        |        |        |                      |       |       |       |                  |       |     |       |                           |               |               |               |
| Insurance                                                             | The Trial is covered by the research insurance of the Balgrist.                                                                                                                                                                                                                                                                                                                                                                                                                                                                                                                                                                                                                                                                                                                                                                                                                                                                                                                                                                                                                                                                        |                            |                            |          |          |             |          |          |          |                              |              |                            |                            |                     |       |       |   |               |       |       |       |                          |        |        |        |                      |       |       |       |                  |       |     |       |                           |               |               |               |
| Monitoring                                                            | The Sponsor Investigator will assign and pay an independent Monitor. The Monitoring is scheduled for three times: begin of the trials, after one year and concomitant to the interim analyses, and at the study end.                                                                                                                                                                                                                                                                                                                                                                                                                                                                                                                                                                                                                                                                                                                                                                                                                                                                                                                   |                            |                            |          |          |             |          |          |          |                              |              |                            |                            |                     |       |       |   |               |       |       |       |                          |        |        |        |                      |       |       |       |                  |       |     |       |                           |               |               |               |

|                                             |                                                                                                                                                                                                                                                                                                                                                                                                                                                                                                                                                                                                                                                                                                                            |
|---------------------------------------------|----------------------------------------------------------------------------------------------------------------------------------------------------------------------------------------------------------------------------------------------------------------------------------------------------------------------------------------------------------------------------------------------------------------------------------------------------------------------------------------------------------------------------------------------------------------------------------------------------------------------------------------------------------------------------------------------------------------------------|
| Storage of data and of the used kits | 
All health-related patient data will be stored for at least 10 years; and archived in the data capture software REDCap™. Hence, the Case Report Form is in electronic form and electronically archived in RedCap. Patient-source data will be registered using subject identifiers. After full data analysis, all subject identifiers will be erased.
 
The decolonization kits will be taken from the patients after use; and counted. After the study, they will be destroyed.
                                                                                                                                                                                                                               |
| Jurisdiction                         | 
The place of jurisdiction is the Canton Zürich, Switzerland.
 
The Donator and the Institution of the Sponsor will make a separate agreement document concerning jurisdiction issues.
                                                                                                                                                                                                                                                                                                                                                                                                                                                                                                                          |
| Publications                         | 
The study team at the Balgrist will present the at least part of the interim results in scientific congresses; and will publish the final results in one or two scientific surgical journals. The Protocol will be published separately, e.g. Journal "Trials".
                                                                                                                                                                                                                                                                                                                                                                                                                                                     |
| Donation                             | 
Schülke & Mayr GmbH will support the study with an unconditional donation of 55,000.- (fifty-five thousand) Swiss Francs (paid in two tranches), which will be used for the salary of the study / infection control nurses, the monitoring and for the Ethical Committee fees. The study team will not make financial profit and cover the minimal operational costs.
 
Schülke & Mayr GmbH will donate all the decolonization kits used for the study, for free (including the corresponding transport costs).
 
Schülke & Mayr GmbH has the rights to consult the data and the draft, but will not be part of the study / academic team that will publish the results of the BALGDEC study.
 |
|                                             |                                                                                                                                                                                                                                                                                                                                                                                                                                                                                                                                                                                                                                                                                                                            |

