### 6.2.1 Method of assignment to treatment/intervention (randomization, stratification)

After written informed consent given participants will be randomized with a 1:1 ratio in either treatment group. Randomization is done by designated study staff drawing a sealed envelope containing a randomization card or electronically. Patients are informed about the assignment by the investigators.

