### **11.2 Determination of Sample Size**

In our hospital, postoperative wound problems occur in at least 5% percent of all interventions. Incidence for both, revision surgery and/or SSI, in our selected patient population is set for 10% according to our clinical experience among the selected patient population that composes our study population.

We perform a superiority RCT with a power of 80% in favor of the decolonization. With 95% event-free surgeries in the decolonization arm versus 90% in the standard arm, we formally need 2 x 474 orthopedic surgery episodes, which we sum up to 2 x 500 surgeries (n = 1'000). A patient can be included several times as long as he/she gets not infected and has not witnessed postoperative wound problems.

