### 11.3 Planned Analyses

All analyses will be performed for the entire study population. In a second step, all analyses will be separately performed according to subgroups of patients, based on the type of orthopaedic surgical procedure (e.g. arthroplasties, implant-related surgeries, etc.). We will use descriptive statistics and will perform group comparisons (using the Pearson- $\chi^2$ -test, the Fischer-exact-test, or the Wilcoxon-ranksum-test), as appropriate. We will also perform composite (SSI and wound problems) and separate (SSI or wound problems) multivariate analysis using a Cox regression model targeting the co-primary outcome variables. For the primary outcome parameter, univariable and multivariable results will be computed using a Cox regression analysis. Variables with a  $p$  value  $\leq 0.2$  in univariate analysis will be included in a stepwise forward selection process for multivariate analysis. Key variables will be checked for co-linearity and interaction. The number of variables in the final model is limited to the ratio of 1 variable to 5 to 8 outcome events. The significance level is  $p \leq 0.05$  (two-tailed).

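### Repeat surgeries of one patient are analysed as independent, with clustering ruled out, so standard errors are not assured to be valid; separately, the adjusted Cox model is selected on the trial's own outcomes

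*Protocol*

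**What the plan says.** Section 11.2 sets the sample size in episodes: "With 95% event-free surgeries in the decolonization arm versus 90% in the standard arm, we formally need 2 x 474 orthopedic surgery episodes". The target is then rounded to 500 per arm, 1,000 in total. On repeat entry the same section states: "A patient can be included several times as long as he/she gets not infected and has not witnessed postoperative wound problems". The participant-number row of the synopsis has a similar rule.

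The Statistical analyses row of the synopsis gives the method: "Multivariate adjustments by Cox regression without cluster analysis", next to Pearson chi-square and Wilcoxon tests. No section provides a robust variance, a frailty term or a first-episode analysis.

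Section 6.2.1 says that "participants will be randomized with a 1:1 ratio in either treatment group", but not what happens when a patient returns for a further episode. Section 11.3.2 defines the intention-to-treat population by patients, although the sample size counts episodes. Follow-up is about six weeks, or one year after implant surgery.

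On adjustment, section 11.3 plans univariable and multivariable Cox results for the primary outcome. Variables with univariate p<=0.2 "will be included in a stepwise forward selection process for multivariate analysis". The final model is capped at one variable per 5 to 8 events. Neither the unadjusted nor the adjusted result is named as primary.

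**The concern.** Two episodes of the same patient share that patient's risk factors. A chi-square test or an ordinary Cox model ignores this. If the patient keeps the arm, the naive standard error tends to be too small and the 5% level is exceeded. The protocol creates the dependence and then excludes the remedy in words, so an analysis plan that followed it would inherit the problem.

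The one-year implant follow-up adds a second difficulty. Re-entry is barred only after an infection or wound problem has occurred, so a second episode can open while the first is still at risk. A later infection could then be counted in either episode or in both, possibly in different arms.

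Covariate selection is a separate matter. When covariates are chosen on the trial's own outcomes, the p-value and interval of the adjusted hazard ratio ignore the selection step. Nothing stated keeps the randomised arm in the model.

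**Working it through.** **Reproducing the plan's figure.** Inputs from sections 11.2 and 11.3: 10% vs 5% events, 80% power, two-sided 5%. With a mean rate of 0.075:

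- n = [1.96 x sqrt(2 x 0.075 x 0.925) + 0.842 x sqrt(0.09 + 0.0475)]^2 / 0.05^2 = 434.4, so 435 per arm.
- With continuity correction: (434.4/4) x [1 + sqrt(1 + 4/(434.4 x 0.05))]^2 = 473.6, so 474 per arm.

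The stated 474 is reproduced exactly, under independent episodes. Power at 500 per arm is 85.2% without the correction.

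**Design effect if a patient keeps the arm.** The share q of patients with two episodes and the intraclass correlation (ICC) are assumptions. DE = 1 + [2q/(1+q)] x ICC, and type I error = 2 x [1 - Phi(1.96/sqrt(DE))].

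- q = 0.1, ICC 0.05: DE = 1 + 0.182 x 0.05 = 1.009; type I error 5.1%.
- q = 0.6, ICC 0.2: DE = 1 + 0.75 x 0.2 = 1.15; type I error 6.8%.

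**Simulation of the unclustered two-proportion test.** Null rate 10%, 1,000 episodes, beta-distributed patient risk, 4,000 runs per cell. The Monte Carlo standard error is sqrt(0.05 x 0.95/4000) = 0.34 percentage points. In the overlap columns the second episode enters whatever the outcome of the first; in the exit columns only if the first had no event.

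| Second episode | ICC | Same arm, overlap | Same arm, exit | Re-randomised, overlap | Re-randomised, exit |
|---|---|---|---|---|---|
| 10% | 0.05 | 5.5% | 5.0% | 4.9% | 4.7% |
| 10% | 0.2 | 5.4% | 5.6% | 5.0% | 4.8% |
| 30% | 0.05 | 5.4% | 4.3% | 4.6% | 4.9% |
| 30% | 0.2 | 6.0% | 5.1% | 4.8% | 4.8% |
| 60% | 0.05 | 5.2% | 4.9% | 4.0% | 4.9% |
| 60% | 0.2 | 6.7% | 5.4% | 4.6% | 5.2% |

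The true standard deviation divided by the naive standard error is 1.02-1.07 (same arm, overlap), 1.00-1.03 (same arm, exit) and 0.98-1.02 (re-randomised). Only the 6.0% and 6.7% cells stand clearly above 5%. The simulation does not model one infection being counted in two episodes; the documents give no basis for its frequency.

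**Power.** The planned 500 per arm absorbs a design effect of 500/474 = 1.055, or 500/435 = 1.149 without the continuity correction. At DE = 1.15 the effective size is 500/1.15 = 435 per arm and power is about 80%.

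**Covariate selection.** Expected events are 500 x 0.10 + 500 x 0.05 = 75. The cap allows 75/8 = 9.4 to 75/5 = 15, so about 9 to 15 data-chosen variables. If the arm were screened like any other variable (an assumption), the probability that it fails p<=0.2 with 500 per arm is 4% at 5% vs 10%, 34% at 7% vs 10%, and 56% at 8% vs 10%. For the first case: standard error under the null sqrt(0.075 x 0.925 x 2/500) = 0.01666, under the alternative sqrt(0.1375/500) = 0.01658, and Phi[(1.2816 x 0.01666 - 0.05)/0.01658] = Phi(-1.73) = 0.042.

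**The case against.** The strongest reply is that the effect on the standard errors may be negligible. Section 11.2 stops re-entry after an event, and with that exit rule the simulated error is 4.3-5.6%. Randomisation is a step of the enrolment visit (sections 9.2 and 9.2.1), and section 11.3.1 counts episodes per randomisation arm. Re-randomisation of each episode is therefore at least as plausible as keeping the arm, and there the error is 4.0-5.2%. This stands as to size. It does not make the plan sound: the arm rule is unstated, and the exit rule does not reach a second surgery performed before the first event appears.

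A reader might infer that the standard errors are plainly wrong. For instance, with 70/20/10% of patients contributing 1/2/3 episodes and an ICC of 0.3, DE = 1 + (2.4/1.4 - 1) x 0.3 = 1.214, type I error is 7.5% and power 78%. That case stacks the same arm, a high correlation, up to three episodes and no exit rule. None of these values is in the protocol, and the last sets aside the re-entry rule in section 11.2.

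A reader might also infer that the treatment estimate as a whole is data-driven. It is not: the two-group tests and the univariable Cox result are untouched by selection. Forcing the arm into a model is also a detail that an analysis plan could settle. What remains is that the protocol states the selection rule for the primary outcome and ranks no analysis above another.

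**Conclusion.** Both points hold as the protocol is written. Ruling out cluster analysis while admitting repeat episodes leaves the standard errors without assurance; neither the size nor the direction of the error can be fixed from the document. Under the assumed ranges it is at most modest: type I error up to 6.7% with the same arm and overlapping follow-up, and close to nominal otherwise. Even at a design effect of 1.15, power by the uncorrected formula stays at about 80%. The 474 per arm is not an arithmetic error.

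The missing rule for assigning an event when two follow-ups overlap is a real gap, with no frequency that can be put on it. The selection procedure affects the multivariable Cox result only, and no bias has been quantified for it. It matters because that result is not declared secondary. The point should be corrected; it does not undermine the design.

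**What to change.** - Replace the exclusion of cluster analysis by a robust (sandwich) variance clustered on patient in the Cox model, and use a cluster-adjusted version of the two-group comparison.
- State whether a repeat episode is re-randomised or keeps its arm, and align the intention-to-treat definition with that unit.
- Attribute each event to one episode only, for example the most recent surgery at that site, with the earlier episode censored at that surgery.
- Add a first-episode-only sensitivity analysis.
- Name one primary analysis.
- For the adjusted analysis, force the arm in and prespecify a short list of baseline variables already recorded or used for eligibility: for example age, implant, type of surgery, diabetes or immune-suppression, and ASA class. ASA appears only among the eligibility criteria, and the listed assessments record osteosynthesis rather than implant as defined in section 3.2.1, so both need a field in the case report form.
- Keep stepwise selection for exploratory risk-factor work.

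The cost is a few lines of text and code, with no extra patients or visits. Intervals may change slightly in either direction. The change should be fixed before outcomes are examined at the one-year interim analysis. Section 2.10 lists some changes to the statistical analysis as substantial, so ethics committee approval may be needed.
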